
## Schedule of Assessments

|                                                                         | Screening Visit                                                                        | Baseline Visit
1 st vaccination                                                                                         | Follow-up Visits                                                                     |                                           |                                                    |                                                                                                                                         |                                                                                      |                                           |                                                    |                                                                                                                                           |                                                                                      |                                           |                                                    |
|-------------------------------------------------------------------------|----------------------------------------------------------------------------------------|---------------------------------------------------------------------------------------------------------------------------------------|--------------------------------------------------------------------------------------|-------------------------------------------|----------------------------------------------------|-----------------------------------------------------------------------------------------------------------------------------------------|--------------------------------------------------------------------------------------|-------------------------------------------|----------------------------------------------------|-------------------------------------------------------------------------------------------------------------------------------------------|--------------------------------------------------------------------------------------|-------------------------------------------|----------------------------------------------------|
| Study weeks                                                             | -1                                                                                     | 1                                                                                                                                     | 1                                                                                    | 2                                         | 4                                                  | 9/10                                                                                                                                    | 9/10                                                                                 | 10/11                                     | 12-14                                              | 26/27                                                                                                                                     | 26/27                                                                                | 27/28                                     | 29/30                                              |
| Study days                                                              | - 7 to -5                                                                              | 1                                                                                                                                     | 3-4                                                                                  | 8-10                                      | 22-27                                              | 57-66 a                                                                                                                      | 59-69 b                                                                   | 64-75 c                        | 78-96 d                                 | 176-187 e                                                                                                                      | 178-190 b                                                                 | 183-197 c                      | 197-213 d                               |
| Examination                                                             | Medical history in-/exclusion criteria pregnancy test (women) written informed consent | Assessment of health status (pre-vaccination)                                                                                         |                                                                                      |                                           | Assessment of health status                        | Assessment of health status (pre-vaccination)                                                                                           |                                                                                      |                                           | Assessment of health status                        |                                                                                                                                           |                                                                                      |                                           | Assessment of health status                        |
| Vaccination                                                             |                                                                                        | 0.5 mL i.m. (left)                                                                                                                    |                                                                                      |                                           |                                                    | 0.5 mL i.m. (right)                                                                                                                     |                                                                                      |                                           |                                                    | 0.5 mL i.m. (left)                                                                                                                        |                                                                                      |                                           |                                                    |
| Blood Sampling Safety (hematology 1c hemistry  ) | 5.5 mL heparin and 2.7 mL EDTA blood                                                   |                                                                                                                                       |                                                                                      | 5.5 mL heparin and 2.7 mL EDTA blood      | 5.5 mL heparin and 2.7 mL EDTA blood               | 5.5 mL heparin and 2.7 mL EDTA blood                                                                                                    |                                                                                      | 5.5 mL heparin and 2.7 mL EDTA blood      | 5.5 mL heparin and 2.7 mL EDTA blood               | 5.5 mL heparin and 2.7 mL EDTA blood                                                                                                      |                                                                                      | 5.5 mL heparin and 2.7 mL EDTA blood      | 5.5 mL heparin and 2.7 mL EDTA blood               |
| Blood Sampling Humoral Immunology                                       | 10 mL full blood (baseline values, incl. Influenza)                                    |                                                                                                                                       |                                                                                      |                                           | 10 mL full blood                                   | 10 mL full blood (pre-vaccination)                                                                                                      |                                                                                      |                                           | 10 mL full blood                                   | 10 mL full blood (pre-vaccination)                                                                                                        |                                                                                      |                                           | 10 mL full blood                                   |
| Blood Sampling T-cell response                              | 25 mL EDTA blood, to be sent to STI within 4 hours                                     |                                                                                                                                       |                                                                                      |                                           | 25 mL EDTA blood, to be sent to STI within 4 hours |                                                                                                                                         |                                                                                      |                                           | 25 mL EDTA blood, to be sent to STI within 4 hours |                                                                                                                                           |                                                                                      |                                           | 25 mL EDTA blood, to be sent to STI within 4 hours |
| Adverse Events (Interviews and diary card)                              |                                                                                        | Baseline AE rate (prior to vaccination) after vaccination 30 minutes observation distribution diary card (self-assessment days 1 – 4) | Picture of injection site, if visible reaction. Recording of AEs check of diary card | Recording of AEs Collection of diary card |                                                    | Baseline AE rate (prior to vaccination) after vaccination 30 minutes observation distribution diary card (self-assessment days 61 – 64) | Picture of injection site, if visible reaction. Recording of AEs check of diary card | Recording of AEs Collection of diary card |                                                    | Baseline AE rate (prior to vaccination) after vaccination 30 minutes observation distribution diary card (self-assessment days 181 – 184) | Picture of injection site, if visible reaction. Recording of AEs check of diary card | Recording of AEs Collection of diary card |                                                    |

 hematology includes: hemoglobin, hematocrite, RBC count, WBC count and differential, platelets count

 blood chemistry includes ASAT/ALAT, alk. Phosphatase, creatinine, CRP

 T-cells will not be assessed in groups PEV 301 10 µg and 302 10 µg

a Should be 9 weeks after the 1st vaccination

b must be 2 (+1) days after vaccination

c must be 7 (+2) days after vaccination

d Must be 21 (+5) days after vaccination

e Should be 26 weeks after the 1st vaccination

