| PROCEDURE                                  | 
Volunteers will be screened, enrolled and followed by the clinical investigator, PD [name] at the Clinical Research Centre of the Kantonsspital Basel.
 
At the screening-visit (days -7 to -5) and after written informed consent has been obtained, the eligible healthy subjects are randomized to vaccination with either three injections of PEV 301 10 µg (Group A) or PEV 302 10 µg (Group B) or PEV 301 50 µg (Group C) or PEV 302 50 µg (Group D) or PEV 301 50 µg plus PEV 302 50 µg (Group E) or virosomes alone (group F) at days 1(+2), 64(+2) and 183(+2).
 
If possible 23 men and 23 women should be enrolled; however, if it is not possible to have an equal sex distribution, the groups can be filled with participants of either sex.
 
The 18 volunteers recruited in October will first be stratified into males and females and then randomized in blocks of 9 (1 block = females, 1 block = males) into 3 groups: Group A (n= 8) will be vaccinated with 10 µg PEV 301, Group B (n = 8) will be vaccinated with 10µg PEV 302, and 2 volunteers will receive virosomes alone (Group F) 5 weeks later again 18 volunteers have to be recruited, they first will be stratified into males and females and then randomized into 3 groups: group C (n = 8) will be vaccinated with 50 µg PEV 301, group D (n = 8) with 50 µg PEV 302, and 2 volunteers will receive virosomes alone (Group F).
 
5 weeks after the 2nd vaccination of groups C and D 10 volunteers will be randomized in blocks of 5 to either group E (n = 8) receiving the combination of 50 µg PEV 301 plus 50 µg PEV 302 or group F (n = 2) receiving virosomes alone.
 
Immunogenicity assessments for humoral immune response are made at baseline (screening blood sample on days -7 to -5), on the days of the 2nd and 3rd vaccination (pre-vaccination samples) as well as 21 (+5) days after each vaccination.
 
Cell mediated immune response will be assessed in groups C, D, E and F only, at baseline (during screening), and 21 (+5) days after each vaccination.
 
Safety assessments are made by the investigator at baseline (before the 1st immunization) and before the 2nd and 3rd immunization as well as 2 (+1) and 7 (+2) days after each immunization.
 
After each immunization the volunteers have to remain in the clinic for a 30 minutes period for the assessment of local and systemic reactions.
 
The volunteers themselves have to fill an adverse event report form (diary card) for a 4 day observation period after each vaccination. Health status will be checked before each immunization, and on days 21 (+5) 85 (+2) and 204 (+2).
 
Standard blood chemistry and hematology will be assessed at the screening visit (days -7 to -5), prior to each vaccination as well as 7 (+2) and 21 (+5) days after each vaccination.
 |                     |                                                                                                                                                          |                 |                                          |

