### **4.2 Inclusion criteria**

The following criteria should be checked at the time of study entry. If any does not apply at the time of study entry, the subject must not be included in the study:

1. Volunteers of both sexes, aged between 18 and 45 years.
2. Written informed consent obtained from the volunteer.
3. Free of obvious health problems as established by medical history and/or clinical examination before entering the study.
4. Body Mass Index between 18.50 and 29.99
5. For female volunteers, a negative pregnancy test and an adequate contraception throughout the study duration.

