### **4.3 Exclusion criteria**

The following criteria should be checked at the time of study entry. If any apply at the time of study entry, the subject must not be included in the study:

1. Use of any investigational or non-registered drug or vaccine within 30 days preceding the first dose of study vaccine, or planned use during the study period and safety follow-up.
2. Chronic administration (defined as more than 14 days) of immunosuppressants or other immune-modifying drugs within six months prior to the first vaccine dose. (For corticosteroids, this will mean prednisone, or equivalent,  $\geq 0.5$  mg/kg/day. Inhaled and topical steroids are allowed.)
3. Any chronic drug therapy to be continued during the study period.
4. Longterm residency in a malaria endemic area in the past
5. Visit to malaria endemic area within 12 months previous to study start
6. Intention to travel to malaria endemic area during the study period
7. History of clinical malaria
8. Any confirmed or suspected acquired immunosuppressive or immunodeficient condition, including human immunodeficiency virus (HIV) infection, or history of congenital or hereditary immunodeficiency.
9. History of allergic disease or reactions likely to be exacerbated by any component of the vaccine.
10. Acute disease at the time of enrolment. {Acute disease is defined as the presence of a moderate or severe illness with or without fever. All vaccines can be administered to

persons with a minor illness such as diarrhea, mild upper respiratory infection with or without low-grade febrile illness, i.e., temperature  $<38^{\circ}\text{C}$  ( $<100.4^{\circ}\text{F}$ )

11. Acute or chronic, clinically significant pulmonary, cardiovascular, hepatic or renal functional abnormality, as determined by physical examination or laboratory screening tests.
12. Acute or chronic diabetes
13. History of chronic alcohol consumption and/or intravenous drug abuse.
14. Pregnant or lactating female.
15. Female planning to become pregnant.

If a subject signs the consent form but withdraws his/her consent after the 1st injection, he/she will abandon the study as of the date of withdrawal. The subject will attest the withdrawal on the consent form and the reason shall be noted at the end of the CRF. Data collected until the date of withdrawal will be used for the statistical analysis of safety.

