### 5.2.1 Screening of potential study participants

During the Screening Visit (days –7 to -5) the investigator has to check whether potential participants for this study meet the inclusion criteria. Volunteers will not be included if any of the exclusion criteria apply. Volunteers who have signed the Informed Consent Form will undergo complete physical examinations, including vitals signs (blood pressure, pulse, temperature) and body systems (cardiovascular, gastro-intestinal, CNS, ENT, respiratory, urogenital, dermatology). Demographic data will be collected, and a complete clinical history will be recorded, and laboratory tests (including HIV and influenza A titer) and a pregnancy test in female volunteers will be performed. In the event that a subject is tested positive for HIV, he/she will be informed and referred for counseling and treatment. Temperature will also be measured daily by the subject and recorded on the diary card provided.

If materials are provided by a centralized laboratory, it is mandatory that all clinical samples (including serum samples) be collected using exclusively those materials in the appropriate manner. The use of other materials could result in the exclusion of the subject from analysis. The investigator must ensure that his/her personnel and the laboratory(s) under his/her supervision comply with this requirement.

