## 8.10 Pregnancy

Subjects who become pregnant during the study period (up to and including one month [minimum 30 days] after receiving the last vaccine dose) must not receive additional doses of vaccine but may continue other study procedures at the discretion of the investigator.

Subjects should be instructed to notify the investigator if it is determined after completion of the study that they became pregnant either during the study or within one month (minimum 30 days) after receiving the last vaccine dose.

A pregnancy should be followed to term, any premature terminations reported, and the health status of the mother and child including date of delivery and the child's gender and weight should be reported to Pevion Biotech Ltd. after delivery.

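### Section 8.10 bars further doses in pregnancy, but the only scheduled pregnancy test is at screening, about 62–73 days before dose 2 and 181–194 days before dose 3

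*Protocol*

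**What the plan says.** **Where a test is scheduled.** The Examination row of the Schedule of Assessments has, in the screening column, "Medical history in-/exclusion criteria pregnancy test (women) written informed consent". No later column names a pregnancy test. Section 5.2.1 agrees: at the screening visit (days -7 to -5) "a pregnancy test in female volunteers will be performed".

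**What pregnancy does to dosing.** Under section 8.10, a subject who becomes pregnant during the study, up to one month "after receiving the last vaccine dose) must not receive additional doses of vaccine". The notification instruction in the same section concerns a pregnancy determined after the study is complete.

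**Other safeguards.**
- Section 4.2 requires "For female volunteers, a negative pregnancy test and an adequate contraception throughout the study duration".
- Section 4.3 excludes pregnant or lactating women (no. 14) and any "Female planning to become pregnant" (no. 15). Both lists of criteria are applied at study entry.
- The Synopsis states "Health status will be checked before each immunization". In the Schedule, the Examination cell for the dose 3 visit is blank.
- Safety blood is repeated at the dose 2 and dose 3 visits, but "blood chemistry includes ASAT/ALAT, alk. Phosphatase, creatinine, CRP". Section 5.3.1 gives the same panel.
- Section 5.2.2 names only the baseline adverse event rate as an assessment before vaccination.
- Section 4.4, on contraindications to repeated vaccination, lists anaphylaxis and immunosuppressive conditions as absolute and acute illness and fever as temporary. Pregnancy is on neither list.

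**The concern.** The protocol treats pregnancy as a reason to stop dosing, yet schedules no way of finding one before doses 2 and 3. As written, the bar in 8.10 takes effect only if the woman already knows she is pregnant and says so. An early pregnancy she has not recognised would pass through the scheduled steps at both visits.

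Section 8.3.1 states that this is the first study of PEV 301 and PEV 302 in humans, and section 1.5 states that volunteers do not benefit directly. What is at stake is an extra dose, in an unrecognised pregnancy, that the protocol itself forbids. No estimate, test or error rate of the trial depends on it.

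**Working it through.** **Inputs.**
- Only pregnancy test: days -7 to -5 (Schedule of Assessments; 5.2.1).
- Dose 1: day 1. Dose 2: days 57–66. Dose 3: days 176–187 (Schedule; 5.2.2).
- Planned women: 23 of 46, if possible (4.1).

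**Age of the test at each dose.** Shortest = earliest dose day minus (-5). Longest = latest dose day minus (-7). If the calendar runs from day -1 to day 1 with no day 0, each interval is one day shorter.

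| Dose | Shortest | Longest | With no day 0 |
|---|---|---|---|
| 1 | 1 + 5 = 6 days | 1 + 7 = 8 days | 5–7 days |
| 2 | 57 + 5 = 62 days | 66 + 7 = 73 days | 61–72 days |
| 3 | 176 + 5 = 181 days | 187 + 7 = 194 days | 180–193 days |

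The narrower +2 day windows in the Synopsis and section 3 (days 64–66 and 183–185) give 69–73 and 188–192 days. The conclusion does not depend on which window is used.

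**Would one extra test be enough?** Dose 2 and dose 3 are 176 - 66 = 110 to 187 - 57 = 130 days apart. A test at dose 2 alone would again be months old at dose 3, so both visits need one.

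**Could an existing step find the pregnancy?**
- Contraception and the exclusion of women planning pregnancy make conception less likely. They do not detect it.
- The entry criteria are checked once, so exclusion no. 14 is not reapplied before later doses.
- The health status check has no stated content and names no pregnancy test.
- The repeated chemistry panel has no pregnancy marker.
- The notification rule in 8.10 covers pregnancies established after the study, when all dosing is over.

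None of these would show an unrecognised pregnancy before the injection.

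**Number of tests.** At the planned 23 women, 23 × 2 = 46. If dose 3 is cancelled for every group under section 10.8, 23 × 1 = 23. Withdrawals, which are not replaced (5.5), reduce it. It is not a ceiling: the Synopsis and 6.3 allow places to be filled by either sex, so more women would mean more tests.

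**The case against.** The strongest reply is that the protocol does have a pregnancy scheme: a negative test and contraception at entry, exclusion of women planning pregnancy, a health check before each injection, a stop on dosing and follow-up to term. It nowhere promises a repeat test, and an investigator may test whenever there is reason to. That is fair, and it rules out one tempting reading, that 8.10 and the Schedule contradict each other. They do not: 8.10 says what to do once a pregnancy is known, and the Schedule does not say how to find one. The gap in detection remains, because testing at the investigator's discretion is not required.

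Other objections, and what stands of them:

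- **Unseen material.** The subject information sheet and CRF are not shown and might add something. An instruction to report a pregnancy would not reveal one the volunteer is unaware of. A repeat test described there would help, but would still need to be in the Schedule.
- **Novel exposure is smaller than 46 doses.** Group F (n = 6) receives virosomes alone, which section 1.4 describes as already used in two registered vaccines. If F were half women (an assumption), 20 women × 2 = 40 doses would carry the new antigens. That matters for exposure, not for the number of tests, since 8.10 does not exempt group F.
- **Blood is already drawn.** The dose 2 and dose 3 columns include "10 mL full blood (pre-vaccination" samples and safety blood, so a reader might infer that a serum test could simply be added. Section 5.3.1 sends safety blood to the hospital's central laboratory and states no turnaround, so a result before injection cannot be assumed.
- **Dose 1 accepts a test 6–8 days old.** True. But no visit falls in the week before dose 2 or dose 3: the preceding visits are at days 22–27 and 78–96. The vaccination visit is the practical place for the test.

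**Conclusion.** The point holds as a gap in detection that is cheap to close. The only scheduled pregnancy test is about 62–73 days old at dose 2 and 181–194 days old at dose 3 (one day less with no day 0), and no other scheduled step would detect an unrecognised pregnancy before those injections. This rests on the Schedule and the protocol text being the full list of required procedures.

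Three stronger inferences are not supported:

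- **A number of exposures prevented.** The protocol gives no pregnancy rate, so none can be estimated. With a small group of women on required contraception, the event should be rare.
- **A demonstrated harm from the vaccine in pregnancy.** The protocol states none. The rule is precautionary, and the avoidable event is a dose given against it.
- **Damage to the trial's results.** The analysis and conclusions are unaffected.

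**What to change.** 1. **Schedule of Assessments:** in the dose 2 (days 57–66) and dose 3 (days 176–187) columns, add a rapid pregnancy test for women, for example on urine, with the result read before injection.
2. **Section 5.2.2:** add the matching sentence, that for women dose 2 or 3 is given only after a negative result that day.
3. **Section 4.4:** list pregnancy as a contraindication to repeated vaccination, so that the section agrees with 8.10.

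The cost is about 46 simple tests at the planned 23 women (23 if no group receives dose 3, otherwise more or fewer with the sex mix and withdrawals), at visits that already take place, plus edits in three places. The protocol gives no unit price. A rapid test makes the change independent of central laboratory turnaround. Sample size and analysis do not change.
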